### ***The use of NASVAC for treating CHB patients was safe and evidenced preliminary efficacy***

In addition, NASVAC therapeutic vaccine candidate has been studied in treatment-naïve chronically infected patients. The formulation -previously studied in healthy volunteers- was administered at 100 mcg per antigen per dose, ten times every two weeks, to HBV chronically infected patients. The formulation was applied -in a first cycle- five times by intranasal route and -in a second cycle-, another five times, simultaneously by intranasal and subcutaneous routes, to the same patients. Patients were characterized as: HBeAg positive (7) and negative (13). ALT baseline levels were normal in 12 patients and abnormal in 8 patients. Patients with antigenemia for more than 6 months and detectable HBV were considered for

treatment after previous altered transaminase determinations in the last six months or by histological abnormalities, recommending treatment.

After dose number ten, there was a 66,6 percent (4/6) of transaminase normalization to levels under the upper level of normality (ULN) for patients starting in abnormal transaminase baseline levels. Biochemical response after treatment largely surpassed the success percentage value required to the clinical trial. Importantly, none of the patients with normal baseline ALT levels had abnormal ALT values after ten doses even when most patients' ALT values peaked during treatment, mainly during the first cycle. The peak after starting therapy has been associated in literature to virological clearance as a result of immune activation in post-treatment period.

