### **Design of the trial**

The population sample to be tested will be of 160 CHB patients, with variable serum transaminase levels, without treatment for at least 6 months, selected according to inclusion and exclusion criteria and allocated in two study groups (SG). The first study group, SG1 will include 80 CHB patients (HBeAg (+) and HBeAg (-)) that will be treated with 1 mL NASVAC (100 mcg per antigen, per dose per patient), administered in two cycles of inoculations, the first one by the intranasal route with five intranasal inoculations every 14 days each. During the second cycle patients will receive the same dosis (100 mcg per antigen) by the intranasal route and additionally the same dosis by the SC route,

The SG2 will be treated with Alpha-Interferon at standard dosis (weekly injection by SC route).

The treatment is discontinued for all patients of SG1 after completion of both cycles. The evaluation will continue during one year, but an interim report will be released after 5 and 10 administrations.

During the whole treatment period up to one year from the beginning of treatment, the systematic assessment of patients is launched to determine to what extent the treatment has driven them to generate the capacity to control the HBV load. This information is included in Figure 1.

[figure not shown]

**Figure 1.** General Algorithm of the trial

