### 5.3 Inclusion criteria

- HBsAg+ serology for more than 6 months before the beginning of the treatment.
- HBeAg (-) patients, with a) baseline HBV DNA  $\geq 10^3$  and b) raised serum ALT ( $> 1 \times \text{ULN}$ ) or significant hepatic necro-inflammation and or fibrosis (HAI-NI $\geq 4$  and/or HAI-F  $\geq 2$ ), or stiffness  $> 7.2$ .
- HBeAg (+) patients, with a) baseline HBV DNA  $\geq 10^4$  and b) and raised serum ALT ( $> 1.5 \text{ ULN}$ ) or significant hepatic necro-inflammation and or fibrosis (HAI-NI $\geq 4$  and/or HAI-F  $\geq 2$ ) stiffness  **$> 7.2$** .
- 18 to 60 years-old patients of both sexes.
- No specific hepatitis B treatment at least for 6 months previous to the inclusion
- Voluntary signed informed consent to participate in the trial

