### **Serology: Response:**

**HBeAg: Negativity:** disappearance from serum

**Seroconversion:** disappearance of HBeAg from serum and appearance of HBeAb.

**HBsAg: Negativity:** disappearance from serum

**Seroconversion:** Appearance of HBsAb in serum.

Both groups will be compared according to the categories defined above by the chi-square test or odds ratio calculation. A logistic regression will be also performed for a multivariate analysis of the influence of the different control variables that result significant in the previous univariate analysis. A signification level of  $p = 0.1$  will be considered. The potency will be of 80%.

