### **Number of patients**

The decision was to take 60 patients per group, 180 patients in total, considering the statistical hypothesis.

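### The 80% power in the serology paragraph has no rate, effect or denominator, and at plausible inputs the design does not support it for the HBeAg endpoints

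*Protocol*

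**What the plan says.** In section 10, the serology paragraph defines four categories: loss of HBeAg, HBeAg seroconversion ("disappearance of HBeAg from serum and appearance of HBeAb"), loss of HBsAg, and HBsAg seroconversion. It continues: "Both groups will be compared according to the categories defined above by the chi-square test or odds ratio calculation". After a sentence on logistic regression it adds "A signification level of $p = 0.1$ will be considered" and then "The potency will be of 80" per cent. No response rate, target difference or denominator accompanies these figures.

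The sample size rests on something else. Under Number of patients: "The decision was to take 60 patients per group, 180 patients in total, considering the statistical hypothesis". The only statistical hypothesis in the protocol concerns undetectable HBV DNA in all patients.

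On who is enrolled, section 4 says "The first study group, SG1 will include 80 CHB patients (HBeAg (+) and HBeAg"-negative, out of 160 in two groups, which leaves 160 - 80 = 80 for the interferon group. Section 5.3 admits both HBeAg types and sets no quota or expected share. It requires every patient to be HBsAg-positive: "HBsAg+ serology for more than 6 months before the beginning of the treatment". The one HBeAg mix in the document is that of the earlier NASVAC patient study in section 2.7: "Patients were characterized as: HBeAg positive (7) and negative (13").

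**The concern.** A patient who is HBeAg-negative at entry cannot lose HBeAg or seroconvert from it. The HBeAg comparisons therefore use only part of each arm, while the trial was sized on an outcome that any patient can reach. One power figure placed over all four serological categories ignores this.

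HBeAg and HBsAg clearance and seroconversion are among the specific objectives in section 2.3, and seroconversion is also compared at the interim analysis. A reader told that these tests have 80% power could take a non-significant HBeAg result as evidence against a worthwhile difference when the design had little chance of showing one.

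**Working it through.** **Inputs from the protocol.** Chi-square test of two proportions; level 0.1 (sidedness not stated, two-sided taken as the natural reading of a chi-square test); 80 per arm (section 4) or 60 per arm (section 10); HBeAg-positive share 7/20 = 35% (section 2.7).

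**Assumptions.** The protocol gives a 20-point difference for HBV DNA only; it is borrowed here. No serological rate is given for interferon, so control rates of 10%, 20% and 30% are tried. A 50% share is tried as a more favourable mix.

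**Step 1: the stated 80%.** It cannot be reproduced, because nothing is attached to it. The nearest match uses all patients as the denominator. With the normal approximation, 20 points and two-sided 0.10, 80 per arm gives 82% (40 v 60%), 83% (30 v 50%), 87% (20 v 40%) and 94% (10 v 30%). With 60 per arm the same cases give 71%, 73%, 78% and 87%. So 80% is plausible only where every patient is at risk.

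**Step 2: patients at risk for HBeAg.** 0.35 x 80 = 28 per arm; 0.35 x 60 = 21 per arm; 0.50 x 80 = 40 per arm.

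**Step 3: exact power.** Sum Bin(x; n, pC) x Bin(y; n, pT) over all pairs (x, y) with |z| > 1.645, where z = [(y - x)/n] / sqrt(2p(1 - p)/n) and p = (x + y)/(2n). This is the uncorrected chi-square test at two-sided 0.10. For the one-sided test at 0.10 the cut-off is z > 1.282.

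| HBeAg-positive per arm | 10 v 30% | 20 v 40% | 30 v 50% |
|---|---|---|---|
| 28 (35% of 80), two-sided | 62% | 51% | 45% |
| 21 (35% of 60), two-sided | 51% | 43% | 37% |
| 40 (50% of 80), two-sided | 75% | 64% | 57% |
| 28 (35% of 80), one-sided | 75% | 65% | 62% |

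Hand check by normal approximation, 28 per arm, 30 v 50%: SE under the null = sqrt(2 x 0.40 x 0.60/28) = 0.131; SE under the alternative = sqrt((0.21 + 0.25)/28) = 0.128; (0.20 - 1.645 x 0.131)/0.128 = -0.12; power = 45%.

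**Step 4: what 28 per arm can detect.** For control rates of 10-30%, 80% power needs a difference of about 27-34 points two-sided, or 22-27 one-sided. Conversely, by normal approximation, 20 points at two-sided 0.10 needs 64 (20 v 40%) to 74 (30 v 50%) HBeAg-positive patients per arm.

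**Step 5: HBsAg.** All patients are HBsAg-positive at entry, so the whole arm is at risk of losing it. With 80 per arm and 20 points, exact power is 81-98% for control rates of 5-40%. With 60 per arm the normal approximation gives 71-93%. Power falls only at smaller, assumed differences: with 80 per arm, 50% for 1 v 5% and 43% for 3 v 8%.

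**The case against.** The strongest reply is that the sentence was never meant for serology. It closes a block that begins with HBV DNA, and it is the only statement of power in the protocol. If it covers serology alone, the main variable has no stated power at all. It may therefore be the trial's general design power, printed in an unlucky place. That reading is possible, but the sentence still sits directly after tests it does not fit, and the remedy is the same: say which comparison it describes.

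Second, no stated figure is strictly contradicted, since the paragraph gives no rates, and 28 per arm does reach 80% power at about 27-34 points. That stands. The fault is an unsupported figure, not a sum that fails to add up.

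Third, the inputs are soft. A share of 7 in 20 has an exact 95% interval of 15-59%, and this trial's entry criteria differ from the earlier study's. Some combinations reach 80%: 47 per arm (59% of 80) at 10 v 30% gives 81%, 40 per arm at 5 v 25% gives 84%, and 28 per arm one-sided at 5 v 25% gives 83%. The protocol commits to none of them.

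Fourth, serology is secondary, section 2.3 describes these data as preliminary, and no interim success criterion rests on them. That limits the consequence.

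A reader might infer that the 80% is wrong for every serological comparison. The documents do not support that: the subset argument does not touch HBsAg loss, and HBsAg falls short at 80 per arm only for differences that appear nowhere in the protocol.

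**Conclusion.** The point holds for the HBeAg endpoints and is conditional. If 35% of 80 per arm are HBeAg-positive, the true difference is 20 points and the control rate is 10-30%, power is about 45-62% at two-sided 0.10, so a real difference of that size would be missed in about 38-55% of trials. With 60 per arm, power is 37-51%. A larger share or a one-sided test raises it, but all the cases in the table stay at or below 75%. These ranges depend on a share from a 20-patient study, an effect borrowed from HBV DNA, assumed control rates and an unresolved arm size. They illustrate the shortfall and are not the trial's established power.

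A reader might also infer that 80% is sound for HBV DNA once it is moved there. Nothing in the protocol shows that. No control rate is stated, and the null hypothesis already allows a difference of up to 20 points, so at a true difference of exactly 20 points the chance of rejecting it is only the significance level.

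**What to change.** Remove the 80% from the serology paragraph. Wherever a power figure is kept, name the comparison, rates, difference, level and sidedness behind it. Do not carry 80% over to HBV DNA unless it is recalculated for the hypothesis as written.

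State that HBeAg loss and seroconversion are analysed in patients HBeAg-positive at baseline. Give their power or detectable difference as conditional on the HBeAg-positive share and on the arm size, after the two sample-size statements are reconciled: section 4 has 160 in two groups, while section 10 has 60 per group and 180 in total, although 2 x 60 = 120. Report these outcomes as differences with 90% confidence intervals, which matches the 0.1 level and shows how much a non-significant result leaves open.

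The cost is a few sentences in section 10 and a less favourable stated figure for secondary endpoints. No patients, visits or assays are added.

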## **Evaluation of the biochemical status**

### **Transaminases: Response**

#### **ALT / AST:**

**Sustained normalization** (reduction to values under 40 IU during a period of three months time) in at least 20% compared to the initial number of patients with altered (more than 40 IU) at the beginning of treatment.

**Normalization:** Reduction to values under 40 IU after one year.

It will be studied for Interim analysis different periods of time and compared to baseline level as described in Interim analysis: after five dosis, after ten dosis, after 24 weeks (6 months) or after 56 weeks (one year)..

The ALT and AST values in serum will be compared between groups and within each group, as quantitative variables, by Student's t or the Mann-Whitney's U test, depending on the normality or not of their distributions. Paired analysis will be also performed within each group to know whether a significant change has occurred in these patients.

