### Treatment schedule

The NASVAC TVC will be administered **to SG1** during the first cycle in a final volume of 1.0 mL (100µg of HBsAg and 100µg of HBcAg) by intranasal route with 8 actuations of 125 µL until completing . The second cycle will continue the IN administration in the same dosis and frequency and simultaneously the same treatment will be administered by the SC route. The device to be used (Valois VP7D spray pump) will be actuated with five minutes intervals between actuations in the same nostril.

The pegylated IFN will be administered **to SG2** weekly by subcutaneous route in the established dose (180µg) .

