#### **Evaluation criteria regarding safety**

All AE that appear during the study will be recorded in the Case Report Form of each individual.

All medical incidents that occur in the first hour after each administration of the vaccine, causally related or not with the vaccination will be recorded.

The rest of the observations will be evaluated in the follow up visits every 14 days.

The observation includes medical questionnaire of the patient, inspection of the injection site, axillary's temperature, and registration of all symptoms and signs referred by the patient. Explanation of how to act in case of abandonment or exit in the trial

The patients that abandon the trial will always be evaluated, except if the investigator loses contact with him. The information will be registered in the Case Report Form (CRF), including the cause of exit.

Quality control of the evaluation procedure

The clinical and laboratory evaluations will be preserved, in order to be examined by external quality controllers.

All primary data should be collected and conserved during the study.

The frequency of specific determinations as well as the type of determination per specific date according to the protocol are presented below: (Grey boxes: Determinations will not be performed).

| Test                    | Baseline
(not more than 2 months before starting treatment) | Week 12 | Week 24
EOT-V | Week 36 | Week 48
EOT-I | Week 72 | Week 96 | Reference Values
(M: male, F: female) |
|-------------------------|----------------------------------------------------------------|---------|------------------|---------|------------------|---------|---------|------------------------------------------|
| Hemoglobin              |                                                                |         |                  |         |                  |         |         | M: 12-17 g/dL
F: 11.5-15.5 g/dL       |
| Hematocrit (PCV)        |                                                                |         |                  |         |                  |         |         | 37-54%                                   |
| Leukocytes              |                                                                |         |                  |         |                  |         |         | 4-10 x 10  /L                |

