In addition, ALT and AST determinations will be conducted after each administration of NASVAC in the corresponding group in order to further study or explore any potential damage.

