### **Interim analysis**

After 5 and 10 administrations and also at 48 weeks, patients will be tested by PCR to quantify HBV DNA in serum as well as for HBsAg and HBeAg seroconversion. A comparative study will be conducted for the same variables for internal comparisons between both groups in order to have a reference to standard treatment with a recognized efficacy.

a) A 20% superior percentage of viral load reduction to undetectable levels in the group treated with NASVAC compared to PegIFN treated group in any of the virological study cuts will be considered as a success criteria for the Interim Analysis.

b) A superior difference in the proportion of patients with ALT normalization or combined ALT normalization and viral load reduction to undetectable levels at a defined time (5, 10 dosis or 48 weeks) between groups will be considered a success criteria for the Interim Analysis.

e) A sustained biochemical (ALT) response during three consecutive determinations after dose number 10 will be considered a success criteria.

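### Sustained ALT response is defined by two unlinked rules that can classify the same patient differently, and neither is tied to time points common to both arms

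*Protocol*

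**What the plan says.** Three statements in Section 10 of the protocol bear on ALT response over time.

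- **Evaluation of the biochemical status, the sustained category:** the criterion reads "reduction to values under 40 IU during a period of three months time) in at least 20% compared to the initial number of patients". The denominator is those whose value exceeded 40 IU when treatment began.
- **Same section, normalization:** "Reduction to values under 40 IU after one year". This is a separate category and not a condition of the sustained one.
- **Interim analysis, item e):** "A sustained biochemical (ALT) response during three consecutive determinations after dose number 10 will be considered a success criteria".

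The measurement schedule comes from Sections 4, 6 and 7.

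- The evaluation table has a baseline column followed by "Week 12 | Week 24 EOT-V | Week 36 | Week 48 EOT-I | Week 72 | Week 96".
- Below that table: "ALT and AST determinations will be conducted after each administration of NASVAC in the corresponding group".
- NASVAC is given in a first cycle of "five intranasal inoculations every 14 days each" and a second cycle at the same frequency. Interferon is given "weekly by subcutaneous route in the established dose".

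**The concern.** Both rules claim to measure a sustained ALT response, but they differ on every element that decides who counts:

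| Element | Sustained normalization | Interim item e) |
|---|---|---|
| Limit | under 40 IU | none stated |
| Duration | three months | three determinations, no minimum time |
| Position in time | none stated | after dose 10 |
| Group bar | at least 20% of those altered at baseline | none |
| Comparator | none | none |

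The protocol does not say which rule governs. The three-month rule does not require a normal value at one year, so a patient can be sustained yet fail plain normalization. The dose-10 anchor belongs to the NASVAC schedule alone, and the extra ALT determinations exist only in that arm. Specific objective 3 includes ALT reduction, item e) is a success criterion, and the trial is open. If the choice between the rules is left until data are visible, the reported result could depend on it.

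**Working it through.** The protocol gives no figure that depends on these definitions, so there is none to reproduce. The check is to list all possible records and score them under both rules.

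**Assumptions.** ALT is measured at every scheduled visit; the shading that would confirm this is not legible in the text available. Three months means two adjacent visits 12 weeks apart. The 40 IU limit also applies to item e). There is no gap between cycles, so dose 10 falls 9 × 14 = 126 days, or 18 weeks, after dose 1. One year is scored at week 48.

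**Scheduled visits to week 48.** Four visits (weeks 12, 24, 36, 48), each normal or raised, give 2⁴ = 16 patterns.

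- Three-month rule (any two adjacent visits normal): 8 patterns.
- Item e) (weeks 24, 36 and 48 all normal, a span of 24 weeks): 2 patterns.
- Three-month rule only: 8 − 2 = 6. Item e) only: 0.
- Of the 8, those raised at week 48: 3 (normal at weeks 12 and 24 only; at 24 and 36 only; at 12, 24 and 36 only).

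Examples, with ALT in IU at weeks 12, 24, 36 and 48:

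| Record | Three-month rule | Item e) | Normal at one year |
|---|---|---|---|
| 36, 35, 60, 70 | yes | no | no |
| 60, 35, 36, 55 | yes | no | no |
| 60, 35, 36, 34 | yes | yes | yes |

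**Visits to week 96.** Six visits give 2⁶ = 64 patterns. The three-month rule is met by 43 and item e) by 16; 27 meet only the former, and 17 of the 43 are raised at week 48.

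**Effect of the NASVAC-only determinations.** Add one value at week 18, after dose 10, to the four visits: 2⁵ = 32 patterns. Scored on scheduled visits, item e) is met by 4. If the week 18 value counts, weeks 18, 24 and 36 also qualify, and 6 patterns meet it. The 2 added patterns are raised at week 48. An interferon patient has no such extra value.

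**Sensitivity to the three-month reading.** If three months needs three visits, because two visits 12 weeks apart fall short of 13 weeks, 3 of 16 patterns meet the first rule and 2 meet item e). One of the 3 is raised at week 48. The gap narrows but does not close.

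These are counts of patterns, not patient rates.

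**Illustration only.** The protocol gives no ALT distribution. Simulated with no treatment effect, assuming baseline ALT above 42, median 50, between-patient log SD 0.5 and visit-to-visit log SD 0.2, the two-visit reading gives 7.9% sustained against 2.5% under item e). The three-visit reading gives 3.3% against 2.5%.

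**The case against.** - **Different quantities?** The first rule speaks of normalization and the second of a biochemical response, in the interim list and without a limit. One could say they were never meant to agree. That is fair as to wording, but both are sustained ALT criteria, the biochemical section itself refers to the interim analysis, and neither states a relation to the other.
- **Any three months.** The protocol does not use the word any; that is a reading of a period with no stated position. The text does not rule it out.
- **Visit mapping.** The weeks at which ALT is measured cannot be confirmed, the resources table in Section 12 budgets 8 ALT/AST determinations per patient, and the biochemical section equates one year with 56 weeks, which is not a scheduled column. The counts therefore depend on the stated grid.
- **Already handled.** One-year normalization has its own category, ALT values are compared between groups, and interim item b) compares the proportion with ALT normalization between groups. This stands: a later relapse would show elsewhere. It does not repair the sustained category.
- **Stronger readings.** A reader might infer that the three-month rule inflates response about three-fold, or that the 20% bar will be met by noise. The documents support neither. The three-fold gap shrinks to about 1.3-fold (3.3% against 2.5%) under the three-visit reading. With 40 altered patients assumed and the two-visit reading, the chance of reaching 8 of 40 with no effect runs from about 0.1% to 12% for medians of 50 to 60 and visit SDs of 0.2 to 0.3. It reaches 34% only at SD 0.4. At the HBeAg-positive ALT entry level (1.5 × 42 = 63 U/L) it is about 0.01% or less over the same range.

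**Conclusion.** The point holds as an unreconciled definition. Two criteria for sustained ALT response differ in limit, timing, duration and bar, and nothing links them. On the stated grid they accept 8 and 2 of 16 patterns, and 3 of the 8 are raised again at week 48. The size of the gap rests on reading three months as two visits, on applying 40 IU to item e), and on ALT being measured at each scheduled visit. That the two rules disagree, and that a patient can be sustained yet not normal at week 48, survives the stricter three-visit reading. The unequal observation of the two arms follows directly from the dose-10 anchor and the NASVAC-only determinations.

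The documents give no ALT rates, so no false-response rate can be attributed to the trial; simulated rates are assumption-dependent illustrations. Nor does the point reach the main result: ALT is a secondary variable, and the HBV DNA endpoint and the sample size are unaffected.

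**What to change.** Use one patient-level rule in both the biochemical section and interim item e):

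1. Population: patients with raised ALT at baseline.
2. One stated limit, applied at fixed scheduled weeks common to both arms.
3. The last of those weeks is the one-year assessment, so that sustained implies normal at one year. State which visit that is, given that the text uses both 48 and 56 weeks.
4. Exclude the NASVAC-only determinations from scoring; keep them for safety.
5. Remove the 20% bar from the definition, and report the between-arm difference in proportions with its confidence interval.

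If weeks 36 and 48 are chosen, state that, by the end-of-treatment labels in the evaluation table, they fall after treatment for NASVAC and up to the end of treatment for interferon. The rule would then describe off-treatment durability in one arm and on-treatment response in the other. Add an analysis at matched times after end of treatment, using the later scheduled visits, if ALT is measured there.

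The cost is rewording two paragraphs and confirming the ALT visits. The reported sustained rate will be lower than under the unanchored three-month rule.

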### **2.4 Reason for which the trial is carried out and background information about the vaccines**

In general, current treatments for CHB are limited in efficacy (around 30% on the basis of some particular criteria). Previous attempts to explore the efficacy of preventive commercial vaccines used for CHB active immunotherapy have also shown a limited efficacy. In this sense, the use of potent adjuvants, new antigens and more immunogenic formulations have been suggested to subvert the immunotolerant status in CHB patients.

The present active immunotherapeutic strategy has been designed to address this problem. This strategy comprises the use of the major HBs and HBc HBV antigens in a novel nasal formulation named NASVAC, characterized by an important cellular and humoral immunogenicity and by the ability to activate both the systemic as well as the mucosal immune compartments in animal models. The proposed approach is considered novel since it has been proven to induce a potent immune response in animal models improving the current state of the art on CHB TVC.

Importantly, NASVAC comprises two antigens:

- a) The r-HBsAg derived from the Cuban *Pichia pastoris* yeast strain transformed by genomic insertion of "s" gene to express r-HBsAg.

This antigen is molecularly identical to that derived from the *Saccharomyces cerevisiae* plasmid constructions used by most of the other vaccines. However, other features were also different for the active antigenic ingredient of the Cuban vaccine, such as a milder purification process (patented) designed to preserve HBsAg-r molecule integrity, including a unique step of preparative

immunoaffinity chromatography (on selective and specific monoclonal antibody). This process is now considered relevant for the higher immunogenicity shown by antigen in preclinical studies and clinical trials around the world. In this sense, the nasal formulation under study -NASVAC- receives the benefit of using the surface antigen with a higher immunogenicity.

- b) The r-HBcAg, the 183 aa. recombinant core antigen (HBcAg) purified and obtained from *E coli* as virus-like particles of around 28 nm with more than 95% purity.

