Further clinical research is required as in case the concept of therapeutic immunization is probed, a large amount of world population will find in therapeutic vaccination a new finite and affordable treatment to overcome current situation.

*All previously presented facts induced the following **working hypothesis**:*

*The administration of NASVAC to CHB patients may subvert tolerance to the surface and core antigens (Ag) of HBV inducing specific immune responses (antibody seroconversion to anti-HBs and anti-HBe), T cells (Th1, CTL) and antigen presenting cells (APCs). Such immune response will favor the control of virus replication and will normalize the transaminases (ALT and AST) in a similar or superior extent to the currently approved treatment Interferon alpha 2b, associated to a lower number of adverse reactions.*

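### The 20% mark for sustained ALT/AST normalisation has no comparator or error rate, so meeting it cannot support the hypothesis of an effect at least matching interferon

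*Protocol*

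**What the plan says.** Protocol section 10, Evaluation of the biochemical status, lists sustained normalisation as a response: values below 40 IU held for three months, "in at least 20% compared to the initial number of patients with altered (more than 40 IU) at the beginning of treatment". The definition of plain normalisation that follows carries no percentage.

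Item e of the Interim analysis section counts a sustained ALT response over three consecutive determinations after the tenth dose as a success criterion. It names no comparison group and no percentage.

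The working hypothesis that closes section 2.7 is comparative. It says the immune response "will normalize the transaminases (ALT and AST) in a similar or superior extent to the currently approved treatment Interferon alpha 2b".

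Groups are compared on other ALT measures. The biochemical section compares ALT and AST between groups as quantitative values. Item b of the Interim analysis section treats a higher proportion with ALT normalisation at a defined time as a success. The chi-square comparison under Serology applies to the categories defined before it, and the transaminase responses are defined after it. None of these covers the proportion with sustained normalisation.

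**The concern.** A response definition should say when a patient has responded. This one also contains a pass mark for the group, set on an observed proportion with no null rate, confidence bound or reference to the interferon arm. Together with item e it invites the report that the sustained biochemical criterion was met, in a two-arm trial whose stated hypothesis is relative to interferon.

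The risk is that reaching 20% is taken as evidence that NASVAC matches or beats interferon on transaminases. Entry criteria favour raised ALT, so some later normalisation can be expected in either arm from regression to the mean. A one-arm proportion cannot separate that from a treatment effect.

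**Working it through.** **1. Does any stated comparison reach this endpoint?**

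| Place in the protocol | Measure | Between groups? | Covers the sustained proportion? |
|---|---|---|---|
| Biochemical status, sustained normalisation | share of altered patients, at least 20% | no | it is the measure, without a comparison |
| Biochemical status, last paragraph | ALT and AST as quantitative values | yes | no |
| Interim analysis, item b | ALT normalisation at a defined time | yes, no test or margin given | no |
| Interim analysis, item e | sustained ALT response | no | yes, without a comparison |
| Serology | HBeAg and HBsAg categories | yes, chi-square or odds ratio | no |

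The sustained proportion is the one ALT response with a numerical mark, and it is the one with no between-group comparison.

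**2. Inputs for an illustration.** The protocol gives no operating figure for this rule, so there is nothing to reproduce.

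- Mark: 20% of patients altered at baseline.
- Number altered, n: not stated; patients enter "with variable serum transaminase levels". Arm size is 80 in the design section ("SG1 will include 80 CHB patients") and 60 in the statistics section ("The decision was to take 60 patients per group, 180 patients in total, considering the statistical hypothesis"). In the earlier study "ALT baseline levels were normal in 12 patients and abnormal in 8 patients", a share of 8/20 = 0.40. That share would give 0.40 × 60 = 24 or 0.40 × 80 = 32. I assume n from 20 to 80.
- True rate, p: not stated for either arm. Section 2.4 says "current treatments for CHB are limited in efficacy (around 30% on the basis of some particular criteria"; it does not name the criterion. I take 30% as one assumed value among several.

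**3. Formula.** The mark is met when X ≥ r, where X ~ Binomial(n, p) and r is the smallest whole number not below 0.20n. For n = 32, 0.20 × 32 = 6.4, so r = 7 and P(X ≥ 7) at p = 0.30 is 0.887.

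| n | r | p = 15% | 20% | 25% | 30% | 40% |
|---|---|---|---|---|---|---|
| 20 | 4 | 0.352 | 0.589 | 0.775 | 0.893 | 0.984 |
| 21 | 5 | 0.197 | 0.414 | 0.633 | 0.802 | 0.963 |
| 24 | 5 | 0.287 | 0.540 | 0.753 | 0.889 | 0.987 |
| 32 | 7 | 0.195 | 0.465 | 0.722 | 0.887 | 0.991 |
| 40 | 8 | 0.244 | 0.563 | 0.818 | 0.945 | 0.998 |
| 60 | 12 | 0.181 | 0.551 | 0.852 | 0.971 | 1.000 |
| 80 | 16 | 0.138 | 0.545 | 0.879 | 0.984 | 1.000 |

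Over every whole n from 20 to 80 the ranges are:

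- true 30%: 0.80 (n = 21) to 0.98 (n = 80)
- true 20%: 0.41 (n = 21) to 0.59 (n = 20)
- true 15%: 0.10 (n = 76, 16 needed) to 0.35 (n = 20)

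**4. Reading.** The interferon rate does not enter the formula. A NASVAC arm at a true 30% meets the mark with the same probability whether interferon achieves 15%, 30% or 40%. The rule responds to NASVAC's own rate and carries no information on the difference between arms.

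**The case against.** The strongest reply is that the 20% stands under a response definition, while the protocol uses the term success criteria elsewhere when it means a decision rule. Controlled ALT comparisons exist in the same section and in item b, transaminases are secondary, the third specific objective seeks only preliminary data on them, and the HBV DNA hypothesis is controlled.

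Much of this stands, and it limits the weight of the point. It does not remove it. Item e does call sustained ALT response a success criterion, and the controlled comparisons concern other measures. An unseen analysis plan could add a test, but the protocol would still carry a mark that cannot bear on its own hypothesis.

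Four stronger readings are tempting and are not supported:

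- A reader might infer that an arm no better than standard care passes about nine times in ten. That treats 30% as interferon's sustained ALT rate. Section 2.4 ties the figure to no named criterion, and no such rate for interferon is given. The 4 of 6 normalised in section 2.7 is a NASVAC result and not the sustained measure.
- A reader might infer that the mark is met whatever the effect. At a true 15% it is met with probability 0.10 to 0.35.
- A reader might hold the rule to a 10% error rate. The 0.1 level is printed in the serology paragraph and is not tied to ALT.
- A reader might call the whole ALT evaluation uncontrolled. Only this threshold and item e are.

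**Conclusion.** The concern holds in a limited form. The 20% mark and item e have no comparator and no error rate, and no stated between-group test covers the sustained proportion. Meeting the mark therefore cannot support a claim of normalisation comparable to or better than interferon. That conclusion follows from the text and needs no assumed rate.

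The size is illustrative only. It rests on an assumed 20 to 80 altered patients and on assumed true rates: 0.80 to 0.98 at 30%, 0.41 to 0.59 at 20%, and 0.10 to 0.35 at 15%. The change should be made, but it concerns a secondary variable and leaves the main HBV DNA comparison untouched.

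**What to change.** - Define sustained normalisation per patient: altered at baseline, then below 40 IU over three months. Delete the 20% as a threshold.
- Among patients altered at baseline, estimate the NASVAC minus interferon difference in proportions with a confidence interval, and fix its level in the same sentence.
- Judge the response at ALT/AST visits common to both arms. Section 7 adds tests after each NASVAC administration in that group only, and unequal testing changes the chance of seeing a raised or a normal value.
- Make item e refer to this contrast. Claim benefit only if the lower limit exceeds 0; otherwise report the difference and interval as descriptive, without concluding that the arms are similar.

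The cost is wording and one contrast on data already collected. The criterion becomes harder to meet, and the estimate is imprecise if few patients are altered. With both arms at an assumed 30% and 32 altered per arm, the standard error is √(2 × 0.30 × 0.70 / 32) = 0.115, so a 95% interval reaches about 1.96 × 0.115 = 0.22 either side. With 80 per arm it reaches about 0.14.
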